   1. GENERAL METHODOLOGY

Quantitative variables will be will be described using the following statistics: number of missing data, mean, standard deviation, quartiles, minimum and maximum values, number and rate of missing variables, and compared between groups with the Mann-Whitney test. No normality check will be performed. Qualitative variables will be reported as absolute and relative frequencies, number and rate of missing variables, and compared between groups with the chi-2 test or the Fisher exact test. Variables will be compared between both groups, except for specific analysis described in 5.2. We will not adjust p-value for multiple comparison. Univariable absolute difference will be reported for each variable as difference [95% confidence interval]. The Hodges-Lehmann method will be used to compute unbiased median differences for outcomes and their CI95%. For qualitative variables, 95% confidence interval will be computed through bootstrapping.

P-value <0,05 with a bilateral hypothesis will be considered as significant. All the analyses will be carried out using R for Windows.

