5.2.4 Daily assessments

Multiple analyses will be performed (methodology described in 5.1)

1. Description of daily assessments for the successful extubation.

The population of analysis will be patients that were successfully extubated. We will report (cf. 4.3):

- - SBT data (on the day of extubation)
  - extubation data
    - Extubation type
    - Post-extubation prophylactic NIV characteristics. Duration of NIV will be computed as the sum of NIV duration on the day of extubation and the following day
    - Post-extubation rescue NIV (during the 7 days following extubation
    - Post-extubation high-flow nasal oxygen (during the 7 days following extubation)
    - Respiratory physiotherapy (during the 7 days following extubation)

Results will be reported a table with four columns (intervention group, control group, p-value).

1. Description of reintubation episodes:

The population of analysis will be patients that experienced reintubation. Since patients can experience multiple reintubations, we will report the number of patients involved and the total number of reintubation. We will not correct for repeated measures. We will report:

- Reintubation data (cf. 4.3)
- Time elapsed since extubation: continuous variable (hours), equals to date/time of reintubation minus date/time of extubation

Results will be reported a table with four columns (intervention group, control group, univariable absolute difference with 95% confidence interval, p-value).

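### The table of reintubation episodes reports confidence intervals and p-values that treat several episodes in one patient as independent

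*Protocol*

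**What the plan says.** Section 5.2.4 of the protocol plans a description of reintubation episodes. Its analysis set is given as "The population of analysis will be patients that experienced reintubation". The section recognises repeated events: "Since patients can experience multiple reintubations, we will report the number of patients involved and the total number of reintubation". It then states "We will not correct for repeated measures".

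The contents are the reintubation data of section 4.3 (the reintubation criterion, five yes/no aetiologies for respiratory reintubation, and reintubation for general anaesthesia of less than 24 hours) and the time since extubation. That time is defined for each episode: it "equals to date/time of reintubation minus date/time of extubation". The table is to include "univariable absolute difference with 95% confidence interval, p-value".

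Section 5.2.4 takes its methods from section 5.1. Quantitative variables are "compared between groups with the Mann-Whitney test", with Hodges-Lehmann differences and intervals. Qualitative variables are compared by chi-square or Fisher's exact test, with bootstrap intervals whose resampling unit is not given. A two-sided p-value below 0.05 is called significant, without adjustment for multiple comparisons.

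**The concern.** The sentence on repeated measures makes sense only if the episode is the unit of analysis, and nothing in the protocol selects one episode per patient. A patient who is reintubated twice brings the same underlying disease, cough and secretions to both episodes, so cause and timing are likely to resemble each other. Pooling then counts partly duplicated information as new, and the stated precision is better than the data support.

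The table carries about eight unadjusted comparisons (1 criterion + 5 aetiologies + 1 anaesthesia item + 1 time). In a trial of 94 patients the reintubated subset may be small, so one or two patients with several reintubations could produce an apparent difference in why or when patients are reintubated. Readers will look at this table when they interpret the reintubation rate.

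**Working it through.** **Plan's own figure.** The protocol states no figure for this table. Its sample size (66 successful extubations, 94 patients) concerns the primary outcome and plays no part here.

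**Inputs.** From the protocol: two-sided 5% level, tests for independent observations, no correction. Assumed, because the protocol does not give them: the number of episodes per reintubated patient (m), the ICC, and the number of reintubated patients per arm.

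**Step 1, approximation with equal numbers of episodes.** The design effect is DE = 1 + (m − 1) × ICC. The naive interval has 1/√DE of its proper width. The true error of a nominal 5% test is 2 × [1 − Φ(1.96/√DE)].

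| m | ICC | DE | Interval too narrow by | True error |
|---|---|---|---|---|
| 1, or any m with ICC 0 | – | 1.00 | 0% | 5.0% |
| 1.3 | 0.5 | 1 + 0.3 × 0.5 = 1.15 | 7% | 6.8% |
| 1.5 | 0.5 | 1 + 0.5 × 0.5 = 1.25 | 11% | 8.0% |
| 2 | 0.8 | 1 + 1 × 0.8 = 1.80 | 25% | 14.4% |

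**Step 2, unequal numbers of episodes.** When counts differ between patients, m is replaced by E[k²]/E[k], where k is the number of episodes in a patient. This exceeds the mean. For example, if 65%, 20% and 15% of reintubated patients have 1, 2 and 3 episodes, the mean is 0.65 + 0.40 + 0.45 = 1.5 and E[k²] = 0.65 + 0.80 + 1.35 = 2.8. The effective value is 2.8/1.5 = 1.87, so DE at ICC 0.6 is 1 + 0.87 × 0.6 = 1.52. Step 1 therefore understates the effect when counts vary.

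**Step 3, simulation of the planned Mann-Whitney test.** There was no true group difference, 12 reintubated patients per arm, 4,000 runs per setting, and episodes treated as independent. The rejection rates at nominal 5% were:

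| Mean episodes | ICC 0 | ICC 0.3 | ICC 0.6 | ICC 0.9 |
|---|---|---|---|---|
| 1.2 | 4.5% | 5.4% | 7.9% | 8.3% |
| 1.5 | 4.7% | 7.0% | 10.7% | 13.1% |
| 2.0 | 4.5% | 8.9% | 14.7% | 18.8% |

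With 8 or 16 patients per arm (2,000 runs each) the pattern was the same: 5.1% to 21.0% for ICC 0.3 to 0.9.

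**Step 4, first episode only.** In the same simulations the test on one value per patient rejected in 3.2% to 5.7% of runs. This agrees with the nominal 5%, allowing for simulation error and some small-sample conservatism.

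**Step 5, price of using the first episode.** With a mean of 1.5 episodes, a first-episode interval is about √1.5 = 1.22 times the naive width. A valid all-episode interval would itself be about √1.26 = 1.12 times the naive width at ICC 0.3 (DE = 1 + 0.87 × 0.3 = 1.26). The real loss is then about √(1.5/1.26) = 1.09, or 9% in width. At ICC 0.6 it vanishes, since DE is already 1.52.

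**The case against.** The best defence is that the table is only a description. It stands under daily assessments, and its items are listed in section 4.3 among the other parameters, not among the primary or secondary outcomes. The choice is disclosed, and patients and episodes will both be counted, so a reader can see how far they differ. With no multiplicity adjustment, nothing in the table could support a confirmatory claim. This stands as a limit on importance, but disclosure does not make the intervals and p-values correct. A purely descriptive table would not need them, and section 5.2.2 already reports baseline data without comparison.

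The size is also uncertain. No document figure supports any value of m or the ICC, and with ICC 0 or one episode each there is no inflation. Most items are categorical, and Fisher's test on small counts is conservative, which offsets part of the effect; the simulation covers only the Mann-Whitney test. All of this stands.

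A reader might infer three stronger things that the protocol does not support:

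- That this is the trial's main safety description. Reintubation rate and mortality are secondary outcomes (section 4.2), and severe adverse events and number of reintubations are tertiary outcomes (section 5.2.5).
- That the conclusion on reintubation is compromised. The secondary reintubation rate counts each patient once.
- That handling the clustering makes this a randomised comparison. The table contains only reintubated patients, a subset formed after randomisation. No choice of episode or resampling scheme changes that, and describing causes of reintubation requires this subset.

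**Conclusion.** The point holds for this one table. The protocol fixes an analysis that treats episodes as independent while acknowledging that they may not be. The direction of the error rests on positive within-patient correlation, which is plausible but not documented. The size rests on assumed values and runs from none to roughly a tripling of the nominal 5% in the less favourable settings. If few patients are reintubated more than once, the effect will be modest. The primary analysis, the sample size, mortality and the patient-level reintubation rate are untouched. It is worth correcting because the text as written would produce invalid intervals and p-values and the correction is nearly free.

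**What to change.** In section 5.2.4, replace the statement on repeated measures with a rule that the between-group difference, 95% confidence interval and p-value use each patient's first reintubation only. Show all episodes beside this as counts and summaries, with the number of patients and of episodes, but without interval or p-value. The simpler alternative is to drop the interval and p-value columns from this table. In either case, add a sentence that the table covers reintubated patients only and that differences are to be read as descriptive.

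Resampling whole patients is a possible third route but is not recommended here. Section 5.1 uses the bootstrap only for qualitative variables, and with few reintubated patients per arm a patient-level bootstrap can itself give intervals that are too narrow.

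The cost is a wording change and trivial programming. Later episodes no longer contribute to the comparison, and the intervals are slightly wider.

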5.2.5 Tertiary outcomes

Analysis will be carried out as described in 5.1.

Tracheostomy data will be reported a table with four columns (overall population, intervention group, control group, p-value) or in text if N<5.

We will report the following tertiary outcomes in a table with four columns (intervention group, control group, univariable absolute difference with 95% confidence interval, p-value):

- - Cause of end of protocol No reintubation in the 7 days following extubation; Withdrawing of care or withholding of reintubation decision; ICU discharge; death; patient still intubated at Day 90.
- Severe adverse event
- Respiratory status at ICU discharge (Day 28, Day 90)
- Successful extubation status
- Successful extubation rank
- Number of reintubation
